## Abstract

**Background:**

Metastatic Breast Cancer (MBC) patients often feel their symptom-related needs are unmet, despite visiting their doctors up to once a week. Novel approaches are needed to address symptoms without requiring additional appointments. Technology based symptom management approaches to address symptoms have not been well tested.

**Methods:**

Nurse AMIE (Addressing Metastatic Individuals Everyday) is a technology based supportive care platform that provides guideline-concordant symptom management interventions in response to patient reported symptoms. We have previously successfully implemented a tablet version of Nurse AMIE. However, some eligible patients chose not to participate because they were overwhelmed by the technology. To address this barrier, we translated the Nurse AMIE platform to the Amazon Echo Show, which allowed for voice-based interactions. Forty-two MBC patients were randomized 1:1 to receive the Nurse AMIE for Echo Show immediately for six months, or to receive the same intervention for three months, after a three month delay. The primary outcome was change in physical distress over three months, and secondary outcomes included feasibility, acceptability, patient reported outcomes and usability.

**Conclusions:**

Results from the Nurse AMIE for Echo Show trial will identify the feasibility, acceptability, and preliminary effects of the Nurse AMIE for Echo Show on patient reported outcomes. Untested novel technologies, particularly voice-based artificial intelligence devices may an effective and scalable vehicle through which we can deliver supportive care interventions.

**Clinicaltrials.gov identifier:**

NCT04673019.

## Introduction

1

Improvements in treatments over the past decade have led to a growing number of metastatic breast cancer (MBC) patients [1]. It is estimated that more than 150,000 women in the United States are living with MBC [2]. Recent research has indicated MBC patients often feel their symptom related needs are unmet, and MBC patients have expressed desire to address these issues to improve their quality of life [3]. MBC patients also expressed that methods to cope with side-effects and symptoms are important informational needs [4,5]. For some MBC patients, the severe side-effects of their treatments reduce quality of life to such an extent that they make decisions to stop treatment, and allow nature to take its course, with a high likelihood of mortality. In this sense, mitigation of side-effects may have survival benefits.

Although MBC patients express desire for more help with symptoms, increased visits to the treatment center can be burdensome; some MBC patients may already have medical appointments as often as once a week [6]. Approaches are required to address symptom needs without additional appointments. Additionally, prior research indicated patients desired a nutrition component be added to Nurse AMIE [7]. Technology may be a useful tool to assess and address the needs of MBC patients, including options to enhance patient-provider communication, and provide guideline-concordant self-care interventions to reduce symptom burden [8]. These technologies take many shapes and forms, and the best ways to use technology to serve the needs of MBC patients are unclear. In prior research, we developed a tablet-based supportive care platform called Nurse AMIE (Addressing Metastatic Individuals Everyday) [8]. It was observed to be feasible and acceptable; patients reported liking the interventions offered on the tablet 83% of the time [8]. However, in this prior work, some MBC patients we approached for the Nurse AMIE intervention declined to participate because they felt overwhelmed by the tablet technology.

## Methods

2

This manuscript adheres to the Standard Protocol Items: Recommendations for Interventional Trials (SPIRIT) Checklist [9]. This investigation was carried out in accordance with the latest version of the Declaration of Helsinki. This study protocol was approved by the Penn State University Institutional Review Board (STUDY00016221).

### Eligibility criteria

2.1

Potential participants were included if they met the following criteria: they were a female patient with MBC, age ≥18 years, had personal, in-home Wi-Fi access, a personal device capable of participating in Zoom calls, fluency in written and spoken English, and sufficient vision/hearing to use the device. Participants were excluded if they had an Eastern Cooperative Oncology Group (ECOG) performance status score >2, significant medical or psychiatric conditions (beyond breast cancer, its treatment, and its symptoms), were receiving any behavioral intervention, were pregnant, had cognitive impairment, or had a life expectancy of less than six months as determined by the treating physician. As MBC patients' conditions are subject to change over time, we sought a second approval from participants’ treating oncologist in the delayed AMIE condition before they started Nurse AMIE to ensure their inclusion/exclusion criteria had not changed during the study. If their treating oncologist indicated they were no longer eligible, we would call the participant and explained this situation to them.

### Recruitment

2.2

Participants were recruited by scanning the electronic medical record of patients seen in the cancer institute to identify potentially eligible women with MBC. Participants were also recruited through social media outreach. The patient's oncologist and/or primary physician provided pre-approval for participants identified from any source. Oncologists at the College of Medicine were also aware of the study, and referred eligible participants to our study staff. We also used a web-based recruitment tool for Penn State researchers, “Penn State Studyfinder” (available at: https://studyfinder.psu.edu), and shared information with national organizations that serve the needs of MBC patients (BreastCancer.org and the Metastatic Breast Cancer Coalition). Research staff approached potentially eligible participants over the phone.

### Study design

2.3

The Nurse AMIE for Amazon Echo Show trial was designed as a partial crossover pilot study with two arms: (1) immediate AMIE and (2) delayed AMIE. The immediate AMIE group received Nurse AMIE for a total of six months. For the first three months, the immediate AMIE group received weekly phone call support from a study facilitator as part of Nurse AMIE. The delayed AMIE group received Nurse AMIE in months four through six only, which included weekly phone call support (Fig. 1).

**Table undtbl1:** 

Group	Support	Months					
		1	2	3	4	5	6
Immediate AMIE	Nurse AMIE						
	Phone call support						

Delayed AMIE	Nurse AMIE						
	Phone call support

**Fig. 1 fig1:**
[figure not shown]
Description of nurse AMIE (Alexa echo show) design.

### Randomization and blinding

2.4

During baseline assessments, participants were randomized using a random sequence generated by a researcher not involved in data collection. Conditions (Immediate AMIE or Delayed AMIE) were blindly placed in sealed envelopes, and not opened until baseline assessments were completed. Randomization was not stratified. Participants were not blinded to their group assignment. Study team members involved in patient-facing work, such as the study-facilitator calls, were also not blinded to group assignment. The principal investigator was blinded to participant allocation, and all study analyses will be performed by study team members blinded to group status.

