### Outcomes

2.15

Patient acceptability was defined as the percentage of eligible and approached participants agreeing to participate in the intervention. We observed an acceptability of 68% with the tablet-based Nurse AMIE intervention, and we hypothesized the Nurse AMIE for Amazon Echo Show version would have a comparable or higher acceptability rate [8]. We defined feasibility the same as the tablet-based Nurse AMIE intervention: participating in at least 30 of the first 90 days. We observed that 86% of our participants in our prior studies that used a tablet version of the intervention achieved this definition of feasibility. We anticipate it would be equally high if not higher with the Amazon Echo Show version.

Patient reported outcomes measures included the 36-Item Short Form Survey (SF-36), the Brief Pain Inventory (BPI), Brief Fatigue Inventory (BFI), PROMIS sleep disturbance measure (PROMIS SF v1.0 - Sleep Disturbance 8b), and a measure of distress used at the Penn State Cancer Institute [[15], [16], [17], [18]]. Outcomes were assessed at baseline, the end of month three, and end of month six. Additionally, assessments related to the usability of Nurse AMIE were collected at the end of month three and six, and included: a User Version of the Mobile Application Rating Scale (U-MARS), System Usability Scale (SUS), Client Satisfaction Questionnaire (CSQ-8), Credibility and Expectancy Questionnaire (CEQ), and Technology Acceptance Model (TAM) [[19], [20], [21], [22]]. Participants completed these outcome questionnaires over Zoom.

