### Sample size

2.16

Based on previous data from the tablet version of Nurse AMIE, the standard deviation for physical distress in MBC patients at baseline was 1.9 units, on a scale of 0–10, and the change over three months was 2.7. To be conservative, we consider the difference of outcome change over three months between two groups as 1.8 (effect size = 0.95). Using a power level of 0.80, and setting (two-sided) α at 0.05, 18 participants per group provided sufficient power to detect the expected between-group difference. Given the potential for disease progression that would prevent continued participation in this population, we anticipated a loss to follow-up of approximately 15%. As such, we recruited 21 participants per group.

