### Statistical analyses

2.18

Data analyses will be performed using SAS version 9.4. Summary statistics including mean and standard deviations for continuous variables and frequency with percentage for categorical variables are reported. The normality assumption for outcome variables is assessed by group based on Shapiro Wilk tests, and the skewness and potential outliers of data distribution will be evaluated to see if any transformation will be needed. Between group (immediate AMIE baseline to month three, and delayed AMIE month four to six) comparison will serve as the primary analyses, where two-sample *t*-tests or Wilcoxon rank sum tests will be used, as appropriate. To further provide evidence informing potential future studies, or may point towards temporal trends or variability in each group, changes within-group (baseline to month three, month four to six) will also be explored mainly with summary statistics. Generalized linear mixed effect models for group comparison will be fitted, and the variables of age, cancer treatment type, and cancer treatment duration will be initially examined and controlled. If we detect some baseline characteristic variables showing unbalanced between two groups, we will consider them in the regression, and report them. The amount of missing data will be reported, which is expected to be minimal due to previous data collection experience. We will try best to collect the data, and report the number of missing data and mechanisms for this missing data (e.g., loss to follow-up, technical errors). If any missing data exist, the missing mechanism will be evaluated. Based on previous work and previous versions of this trial on the tablet, it is reasonable to assume that data will be missing at random (MAR), under which the likelihood based analyses will yield valid estimates and valid inference.

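### The claim that every analysis is done blinded to group conflicts with a primary comparison that uses a different time window in each arm

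*Protocol article*

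**What the plan says.** **Blinding.** Section 2.4 (Randomization and blinding) says that participants and patient-facing staff know the allocation and that the principal investigator does not. It adds, without qualification, that "all study analyses will be performed by study team members blinded to group status".

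**Design.** Section 2.3 (Study design) says "The immediate AMIE group received Nurse AMIE for a total of six months", whereas "The delayed AMIE group received Nurse AMIE in months four through six only".

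**Assessment times.** Section 2.15 (Outcomes) gives one schedule for the patient-reported outcomes, with no distinction by arm: "Outcomes were assessed at baseline, the end of month three, and end of month six". Usability questionnaires are collected at months 3 and 6. Feasibility is use on at least 30 of the first 90 days.

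**Primary outcome and analysis.** The abstract states: "The primary outcome was change in physical distress over three months". Section 2.18 (Statistical analyses) then says: "Between group (immediate AMIE baseline to month three, and delayed AMIE month four to six) comparison will serve as the primary analyses". It also says that "changes within-group (baseline to month three, month four to six) will also be explored mainly with summary statistics". The same section leaves three choices until the data are seen: whether to transform, whether to use a t-test or a Wilcoxon rank sum test, and which unbalanced baseline variables to consider in the regression.

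**The concern.** An analyst who must take one calendar window for one group and a later window for the other has to know which group is which. On its face, the primary analysis therefore cannot be run as worded by someone who is blinded in the sense of section 2.4.

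Two published rules conflict here; this is not a matter of missing detail. Participants and patient-facing staff are unblinded and the outcomes are self-reported, so analyst blinding is one of the few remaining protections that the article names. What it would protect are the data-dependent choices in section 2.18. If the conflict stays, readers will credit the primary result with a safeguard that the stated analysis defeats.

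**Working it through.** **1. The plan's own figures.** The inputs, from section 2.16 (Sample size), are a between-group difference in change of 1.8, a standard deviation of 1.9 ("the standard deviation for physical distress in MBC patients at baseline was 1.9 units"), power 0.80 and two-sided α 0.05.

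- Standardized effect: 1.8 / 1.9 = 0.947, stated as 0.95.
- n per group = 2 × (1.960 + 0.842)² × (1.9 / 1.8)² ≈ 17.5, rounded up to 18. This matches the article.
- Power at 18 per group is 81.1% by the normal approximation and 78.8% by the t distribution.
- Attrition: 18 × 1.15 = 20.7, which rounds up to the stated 21. Dividing instead gives 18 / 0.85 = 21.2, or 22. The difference is small.

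None of these figures depends on blinding. What matters here is that the calculation rests on the difference between groups in change over three months.

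**2. Can each analysis be run under a coded A/B label?**

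| Analysis | What it needs | Does the code hide the arm? |
|---|---|---|
| Primary distress comparison as worded in section 2.18 | With visits at baseline, month 3 and month 6, apparently month 3 minus baseline in one arm and month 6 minus month 3 in the other | No. The analyst must be told which code takes which window |
| The same outcome, baseline to month 3 in both arms | Month 3 minus baseline for everyone | Yes |
| Feasibility | Days of use | No, from a dated log: the delayed arm has no use in months 1 to 3 |
| Usability at month 3 | Questionnaires about the system | No. The delayed arm has not yet had it, so its answers, or their absence, give it away |

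The first two rows differ only in the window. The delayed start is common to both, so it is not what breaks the blinding of the distress comparison. The last two rows follow from the delayed start itself, and changing the primary window does not repair them.

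The within-group summaries are ambiguous. If one window per arm is meant, they reveal the arm as the primary comparison does. If both windows are meant for both arms, a code could hold until use or usability data are attached.

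**3. How much choice is exposed?** Leaving covariates aside, the change score can be analysed by a t-test untransformed, a t-test transformed, or a Wilcoxon test. That is three results, because the rank sum test is unchanged by a monotone transformation of the change score. Four would require transforming the raw scores before differencing, and section 2.18 does not say which is meant. The choice of unbalanced covariates comes on top.

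**The case against.** The strongest reply is that blinding remains achievable. Someone other than the analyst could derive one change score per patient and pass it on under masked labels; the Shapiro-Wilk, t and Wilcoxon steps would then need no arm identity. Who derives and releases datasets is something an article commonly leaves to the full protocol or analysis plan, which are not shown. This stands against a stronger reading that a reader might infer, namely that blinding is impossible. The documents do not support that. They support only that the procedure as published conflicts with the claim as published. Such a step would also leave use and month 3 usability data revealing the arm, so a claim covering all analyses would still be too broad.

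A reader might also infer that any delayed-start design defeats analyst blinding. The common assessment schedule in section 2.15 contradicts that for distress.

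Three further replies carry weight:

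- The analysis choices are tied to normality tests, skewness and outliers, so they are not wholly free.
- Feasibility is a proportion set against a prior 86%, with no between-arm test described, so blinding protects little there. Days of use could also be counted from each participant's own start.
- The article has other safeguards that this point leaves untouched: a sequence generated by someone outside data collection, sealed envelopes unopened until baseline is complete, and a blinded principal investigator.

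Finally, comparing the two arms during their treated periods raises a separate and more serious question about what the primary analysis estimates. If that window is changed, most of the blinding conflict in the primary analysis goes with it.

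**Conclusion.** The conflict is real and should be corrected. As worded, the section 2.4 claim does not hold for the primary comparison in section 2.18, nor for analyses that use device logs or month 3 usability data. An analyst applying the windows knows the group of all 42 participants while choosing among at least three forms of the primary test, before covariates.

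The consequence is modest. The larger source of bias is self-report by unblinded participants, which analyst blinding would not remove. No bias or error inflation has been estimated, and no sample-size figure changes. A reader might infer that the primary result will be biased by its analysts; the documents do not show that.

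The conclusion assumes that the delayed arm's window runs from the month 3 to the month 6 assessment, the only visits listed that fit, and that no undisclosed masking step exists. If one does exist, the primary test could be protected, but the unqualified claim would still need narrowing.

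**What to change.** In section 2.18, state the primary comparison as change in physical distress from baseline to month 3 in both arms. This agrees with the primary outcome in the abstract and with the basis of the sample size in section 2.16. Then:

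1. Give the analyst a file with only baseline and month 3 patient-reported outcomes, baseline covariates and arm coded A/B.
2. Lock the transformation, test and covariate choices, and the month 3 distress result, before releasing device-use, usability and month 6 data and breaking the code.
3. In section 2.4, limit the blinding claim to that analysis and say that the feasibility, usability and month 4 to 6 analyses are unblinded.

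If the arm-specific window is kept, state that someone other than the analyst derives one change score per patient and supplies it under masked labels, and narrow section 2.4 in the same way.

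The cost is text changes in both sections (an edit to section 2.4 alone would not be enough), a data-release order and a narrower blinding claim. No new data are needed. Section 2.18 describes the analyses as still to be performed, so the order of release can still be set.

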### Translating the tablet-based nurse AMIE to the Amazon Echo Show

2.5

The Amazon Alexa ecosystem uses audio processing and machine learning for understanding voice commands and inputs from users. It also provides an Application Programming Interface (API), which can be used to develop a highly customized and context-aware dialogue system (“skill”). In this project, we leveraged the API to develop Nurse AMIE as an Alexa skill. More specifically, we provided the following functionalities to MBC patients: i) voice interface; ii) dynamic information delivery; iii) collection of data from patients (e.g., step counts; symptoms); and iv) sharing data with facilitators and clinicians. We describe these functionalities in detail below.

### Voice interface

2.6

Voice interface allowed users to interact with the device using just speech and audio commands. Voice interfaces enable interactive, engaging, and dynamic delivery of content. To develop the Nurse AMIE for Amazon Echo Show voice interface, we adapted the existing content from the tablet version of Nurse AMIE. This involved determining message content, identifying turn-taking points, and establishing potential branching based on inputs from a participant. We also focused on smart and dynamic handling of conversations to adapt to different user-initiated scenarios and contexts. This resulted in a personalized “virtual coach,” that reflected participants’ unique needs and interaction styles. The user speaks to the Echo, says “Open Nurse AMIE,” and the program opens. The screen depicts a nurse in a lab coat and Nurse AMIE verbally greets the participant and provides a nutrition tip. Nurse AMIE then asks the participant symptom questions. The participant answers, just like she is speaking with a human nurse. Based on the answers the participant provides, Nurse AMIE gives an intervention to help those symptoms.

To develop the voice interface, we adopted an iterative process. In the first phase of this process, we developed a set of decision trees (“flow diagrams”). In these decision trees, branches indicate different interaction pathways following user responses. These decision trees provided the blueprint for user interface and navigation in the Alexa skill. During the development phase, we followed established design guidelines for effective voice interactions (e.g., supporting quick interaction turns, and being adaptable). We also conducted in-lab usability tests with small samples of patients and stakeholders to ensure the voice interface is robust, easy to navigate, and highly useable [10].

### Dynamic information delivery

2.7

Dynamic content changes based on the behavior, preferences, and interests of a user. The dynamic content is personalized and adapts based on the data from the user. The goal of the dynamic information delivery is to provide an engaging and satisfying experience. Dynamic information delivery is generally powered by applications and scripts, working in tandem with static content. Examples relevant to the Nurse AMIE Alexa Skill might be responses to fatigue (Fig. 2). Fatigue is a common issue in MBC patients. To address fatigue, the Alexa skill could provide dynamic guidance. For example, participants were asked about their fatigue level every day as one of the daily questions (other questions probed sleep, distress, and pain). In response to high fatigue, patients were provided with walking step goals and exercise videos. Participants could use audio commands to start these services at any time, without waiting for the daily greeting and daily symptom question. Furthermore, the skill provided a variety of services, including video interventions aiming to help with coping with symptoms. The skill also provided guided relaxation recordings and soothing music.

